#### Power calculations

Prior to this exploratory trial, the means and standard deviations of the main behavioural outcomes were estimated in the pilot study, based on previous Dutch studies to perform a power analysis for determining the study’s required sample size. As stated in literature, a ‘generic’ target of 10–15% points of detectable change suits a program such as this UHS-exploratory trial [46]. As stated by Babyak, for multiple regression analyses 15 persons/observations per parameter are to be included in the measurements for conservative power calculations [47]. With an expected response rate of >90% and 30 included parameters to be measured, a sample size of approximately 500 observations is required for a power of 0.80 at an alpha-level of 0.05 for statistical significance, whilst approximately 1500 students are expected to participate in the study. The sample size thus exceeds the needed requirements, but was chosen to guarantee the study results being sufficiently representative and to allow for sub-group analyses.

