## Introduction

Unhealthy behaviours such as alcohol use, smoking, unhealthy nutrition or excessive time spent behind screens (e.g. the television, computer or game console) show alarming trends in The Netherlands and the rest of the developed world [1, 2]. Children and adolescents are a particularly vulnerable subpopulation in this respect, with half of all adolescents being involved in *at least* one or more unhealthy behaviours [3]. Many of these unhealthy behaviours are known to originate in adolescence and consequently pose a gateway to poor adult health [4]. Moreover, recent literature suggests that these behaviours act as being associated with each other instead of acting independently. In several recent studies this clustering is hypothesized to act on one’s health interactively, i.e. individual behaviours yield greater effects when present together than their individual sums would be expected to [1, 5–8].

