**Figure 3 fg003:**
[figure not shown]
A summary of Guggleberger and Dür’s needs of schools and the capacity building measures for schools for Health Promoting School implementation [50].

**Table 1 tb001:** Variables measured in the questionnaire.

Factor	Operational variable
School level	
School	Coded: 1, 2, 3 or 4
Individual/student level	
Socio-demographic characteristics	
Ethnicity*	Dutch, Moroccan, Turkish, Surinamese, Netherlands Antilles, other.
Socio-economic status*	Family affluence scale (FAS) [39]
School level*	Level 1 (‘VMBO’) to level 3 (‘VWO’)
Age*	
Gender*	M/F
Behaviour	
Ever alcohol use*	Yes/No
Recent alcohol use*	Yes/No
Frequency of recent alcohol use*	‘Number of times ever’/‘Number of times per month’
Ever smoked*	Yes/No
Active smoker*	Yes/No
Frequency of smoking*	‘Number of times per week’/‘Quantity per week’
Ever cannabis use*	Yes/No
Recent cannabis use*	Yes/No
Frequency of cannabis use*	‘Number of times ever’/‘Number of times per month’
Breakfast habits*	Number of days per week
Fruit consumption*	Portions per week
Vegetable consumption*	Number of days per week
Physical activity*	At least on average one hour a day moderate to intense physical activity
Recent bullying*	More than once per month
Recent, frequent bullying*	More than once per week
Recent being bullied*	More than once per month
Recent, frequent being bullied*	More than once per week
Ever had intercourse*	Yes/No
Age of first intercourse debut*	Age of student
Contraceptive use behaviour*	Range from ‘Always’ to ‘Never’ (5 point Likert scale)
Ever had STD*	Yes/No/Unsure
Time spent watching television*	Hours per week
Time spent on pc/internet*	Hours per week
Compulsive pc/internet use	Compulsive internet use scale (CIUS) [40]
Time spent (online) gaming*	Hours per week
Compulsive (online) gaming	Videogame addition test (VAT) [41]
Health outcome	
Physical health*	Body mass index (BMI)
Psychosocial health	Strengths and difficulties questionnaire (SDQ)* [42, 43]
	Self efficacy measure [44]

*Variables directly based on the Dutch HBSC questionnaire.

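### The 15-per-parameter rule counts all students, but for the 12 to 13 Yes/No-type outcomes in Table 1 the smaller answer category is what limits the model, so the claim that the sample is more than sufficient is not shown for them

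*Protocol article*

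**What the plan says.** The Power calculations section rests on one rule, a count of persons: "for multiple regression analyses 15 persons/observations per parameter are to be included in the measurements for conservative power calculations". It combines this with "30 included parameters to be measured" and a response rate above 90%, and states that "a sample size of approximately 500 observations is required for a power of 0.80 at an alpha-level of 0.05". About 1500 students are expected, and the section concludes: "The sample size thus exceeds the needed requirements". The surplus is justified partly by planned sub-group analyses. The target change is expressed in percentage points (10–15). Nothing in the section separates continuous from Yes/No outcomes.

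The section on main outcomes, under Data analysis, applies multilevel regression and ANCOVA to health behaviours and health outcomes generally. Table 1 lists 26 behaviour rows and 3 health outcomes, 29 in all. Twelve are two-valued:

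- seven Yes/No items (for example "Ever cannabis use");
- four bullying thresholds;
- one physical-activity threshold.

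The STD item is Yes/No/Unsure.

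**The concern.** A person count per parameter is a guard against overfitting when the outcome is continuous. When the outcome has two values, a thousand students of whom fifty answer yes say little more about a coefficient than the fifty do. Information on a log-odds coefficient is proportional to N·p·(1−p), which for an uncommon answer is close to the number giving that answer. For example, 1350 × 0.05 × 0.95 = 64.1, against 67.5 students in the smaller category.

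Behavioural change is the main outcome of the study, and 12 or 13 of its 29 outcomes are of this kind. An unqualified statement that the sample is more than sufficient could be read as licence to fit the same full covariate model to every outcome. For an uncommon outcome, the coefficients of such a model, including the one for the intervention, could be overfitted or, in a logistic model, biased away from zero.

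**Working it through.** **Inputs.** From Power calculations: 15 observations per parameter, 30 parameters, response above 90% (taken as 90%), about 1500 students. From Table 1: the outcome types. The article gives no prevalences, so they are left free.

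**The plan's own figure.** 15 × 30 = 450 respondents, and 450 / 0.90 = 500 to be approached. This reproduces the stated 500.

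**Same threshold, counted on the smaller category.** For N respondents, prevalence p and k coefficients, the condition is N × min(p, 1−p) ≥ 15k, so p must lie between 15k/N and 1 − 15k/N. If 15k/N exceeds 0.5, no prevalence meets it.

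Three model sizes are used:

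- k = 30, if the 30 parameters are coefficients of one model: 450 needed in the smaller category.
- k = 12, an assumed model with arm 1, baseline 1, ethnicity 5, family affluence 1, school track 2, age 1 and gender 1: 180 needed.
- k = 7, the same model with ethnicity and track each reduced to one term: 105 needed.

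The values of N are 450 (500 approached), 1350 (1500 × 0.90) and 1500 (if 1500 already means respondents).

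| Respondents | k = 30 | k = 12 | k = 7 |
|---|---|---|---|
| 450 | none | 40–60% | 23.3–76.7% |
| 1350 | 33.3–66.7% | 13.3–86.7% | 7.8–92.2% |
| 1500 | 30–70% | 12–88% | 7–93% |

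For the 'none' cell, the most that 450 respondents can supply is 450 / 2 = 225, which is 225 / 30 = 7.5 per coefficient, half the threshold.

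**Coefficients supported by 1350 respondents**, from 1350 × p / 15:

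- 20%: 270 / 15 = 18
- 10%: 135 / 15 = 9
- 5%: 67.5 / 15 = 4.5, so 4

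With 1500 respondents these become 20, 10 and 5.

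**Sub-groups.** If the three school tracks were equal in size (an assumption), each would have 1350 / 3 = 450 respondents. The two track terms drop out, leaving 10 coefficients and 150 needed. The condition then holds for 150 / 450 = 33.3% to 66.7%. The surplus is thinnest where the plan intends to use it.

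**The case against.** Several points on the other side are sound.

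- A reader might infer that the plan breaks its own rule. It does not. The rule counts persons, and 450 respondents from 500 approached meet it exactly. Counting the smaller category is a general principle that the article does not state.
- A reader might also infer that 500 can never be enough, or that 1500 is enough only between about one third and two thirds. That needs all 30 parameters in every Yes/No model. The phrase "30 included parameters to be measured" may mean questionnaire variables, and no 30-coefficient model is described. With 12 coefficients 450 respondents can suffice, and 1350 cover a wide range.
- The article says 1500 will participate, so a further 10% deduction may be wrong. Both figures are shown above.
- The survey is annual, so observations may outnumber students. Repeated answers from one student are correlated, however, and add less than new students would.
- No logistic model is named. A linear model for a 0/1 outcome would avoid the logistic small-sample bias, though few events would still carry little information.
- The Introduction's statement about "half of all adolescents being involved in" one or more unhealthy behaviours cannot be turned into prevalences for single items. That would require equal and independent behaviours, and the Introduction says they are associated.

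It can also be argued that covariate lists and sparse-outcome methods belong in the full protocol or analysis plan. That is fair for those details. It does not cover the printed calculation and the unqualified conclusion drawn from it, which are in this article.

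**Conclusion.** The point holds in a limited form. The arithmetic behind 500 is correct as a person count, but that count is the wrong quantity for 12 two-valued outcomes and the STD item, so the sufficiency statement is not established for them. How far it fails depends on two things the article does not fix: the number of coefficients per model and the prevalence of each outcome. Common outcomes with moderate models are well served by 1350–1500 respondents. An outcome at 10% supports about 9 coefficients from 1350 respondents and one at 5% about 4, well short of 30 and also short of the assumed 12. Whether any particular item, such as cannabis use or weekly bullying, is that uncommon in these schools cannot be read from the article.

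This stands even if the rule is taken only as a guard against overfitting. Two other matters are separate: the 500 uses neither the target effect nor the stated power and alpha, and no figure here allows for clustering in four schools.

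**What to change.** In Power calculations:

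- Confine the person-count rule, and the statement that the sample exceeds what is needed, to continuous outcomes.
- Say whether the 30 parameters are coefficients of one model or measured variables.
- For Yes/No outcomes, state the number required in the smaller category and the prevalence range in which the expected sample supplies it.
- Keep the coefficients in each Yes/No model within the smaller-category count divided by 15, for example by collapsing ethnicity and school track.
- Where even the minimum model exceeds that limit, use penalised (Firth-type) regression or report the outcome descriptively.
- Apply the same limit within sub-groups.

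The cost is one reworded paragraph and a limit on model size; the sample need not change. The drawbacks are coarser covariate adjustment for uncommon outcomes and a less favourable sample-size statement.

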## Methods

### Study design: an exploratory trial

The UHS remains similar in terms of format, content and implementation as the pilot, only targeting different schools in a different study setting. It will be implemented on two Dutch secondary schools, with two comparable schools serving as controls (n≈1500 students) in an exploratory trial study design [33].

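### The 500 observations said to give 80% power come from a regression model-size rule, not a power calculation, and ignore that only four schools carry the comparison

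*Protocol article*

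**What the plan says.** The Power calculations section of the protocol article cites a rule that "for multiple regression analyses 15 persons/observations per parameter are to be included in the measurements for conservative power calculations". It then gives its inputs, "With an expected response rate of >90% and 30 included parameters to be measured", and states that "a sample size of approximately 500 observations is required for a power of 0.80 at an alpha-level of 0.05 for statistical significance". About 1500 students are expected, and the section concludes: "The sample size thus exceeds the needed requirements". It justifies the excess by representativeness and by room for subgroup analyses.

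The same section names an effect target ("a ‘generic’ target of 10–15% points of detectable change suits a program such as this UHS-exploratory trial") and says that "the means and standard deviations of the main behavioural outcomes were estimated in the pilot study", but gives no baseline rate, mean or standard deviation. It does not mention schools, an intraclass correlation or a design effect.

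Elsewhere, the study design section assigns the intervention to "two Dutch secondary schools, with two comparable schools serving as controls". The section on main outcomes under Data analysis plans multilevel models with a school level and a student level.

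**The concern.** There are two separate faults.

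- **The 500 is not a power calculation.** A rule on observations per parameter protects a regression model from overfitting. It cannot yield a power at a given alpha, because neither the effect to be detected nor the variability of the outcome enters it.
- **The sum counts students as if they were independent.** The intervention is given to whole schools, two per arm, and the planned analysis recognises this. Comparing 1500 clustered students with a threshold that has no clustering term does not show that the sample is sufficient.

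Readers are told that the trial has at least 80% power for a 10–15 point change. A null result could then be taken as evidence of no effect when the design had little chance of showing one. The planned subgroup analyses rest on the same claimed surplus.

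**Working it through.** **Step 1: reproduce the stated figure.** Inputs from the Power calculations section: 15 observations per parameter, 30 parameters, 90% response.

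15 × 30 = 450; 450 / 0.90 = 500.

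This matches exactly. Alpha, power, the 10–15 point target and the pilot means and standard deviations are not used.

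**Step 2: the power that 500 independent students give.** Take 250 per arm and a two-sided alpha of 0.05 (the article does not state sidedness). Power = Φ[(Δ − 1.96·√(2p̄(1−p̄)/n)) / √((p₁(1−p₁)+p₂(1−p₂))/n)]. For 50% versus 40%: (0.100 − 1.96 × 0.0445) / 0.0443 = 0.29, so power is 0.61. The baseline rates are assumptions.

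| Difference | Power at 500 | Total n for 80% power |
|---|---|---|
| 50% vs 40% | 0.61 | 776 |
| 30% vs 20% | 0.73 | 588 |
| 20% vs 10% | 0.88 | 398 |
| 50% vs 35% | 0.93 | 340 |
| 30% vs 15% | 0.98 | 242 |

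So 500 does not correspond to a power of 0.80. The result depends on an unstated baseline and on which end of the 10–15 point range is meant.

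**Step 3: put the four schools in.** Assumptions: equal schools, 1500 / 4 = 375 students each; standard deviation at 30% prevalence, √(0.3 × 0.7) = 0.458; ICC from 0.005 to 0.05, since the article gives none.

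- Design effect = 1 + (375 − 1) × ICC; effective n = 1500 / design effect.
- Standard error of the arm difference, two schools per arm = 0.458 × √(ICC + (1 − ICC)/375).
- Degrees of freedom for a school-level contrast = 4 schools − 2 arms = 2. The two-sided 5% critical value of t is 4.30, and 80% power needs a difference of about 5.66 standard errors (non-central t).

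For ICC 0.01: design effect 4.74; effective n 1500 / 4.74 = 316; standard error 0.458 × √0.01264 = 0.0515; detectable difference 5.66 × 0.0515 = 0.29.

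| ICC (assumed) | 0.005 | 0.01 | 0.02 | 0.05 |
|---|---|---|---|---|
| Design effect | 2.9 | 4.7 | 8.5 | 19.7 |
| Effective n of 1500 | 523 | 316 | 177 | 76 |
| Power, 10 points, normal test | 0.70 | 0.49 | 0.31 | 0.16 |
| Power, 10 points, 2 df | 0.30 | 0.21 | 0.14 | 0.09 |
| Power, 15 points, normal test | 0.96 | 0.83 | 0.59 | 0.30 |
| Power, 15 points, 2 df | 0.52 | 0.37 | 0.25 | 0.14 |
| Detectable at 80%, 2 df (points) | 23 | 29 | 39 | 59 |

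Effective n falls to 500 when the design effect is 1500 / 500 = 3, that is at ICC = 2 / 374 = 0.0053.

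**Step 4: would more students help?** With unlimited students per school, power on 2 df for 50% versus 40% is still only 0.22 at ICC 0.01 and 0.14 at ICC 0.02. The limit is the number of schools.

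**The case against.** The strongest points on the other side are these.

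- **The sum itself is correct.** 15 × 30 / 0.90 is 500. The error lies in calling the result a power calculation and in what is concluded from it. That is a fair clarification, and it does not save the statement.
- **The target reaches up to 15 points.** For 15 points, 500 independent students give 0.93 or more at the baselines shown, and a 12.5-point fall from 50% gives 0.81. So before clustering, 500 is not far from 80% power for part of the target. This is a coincidence of the chosen baseline, not a result of the derivation.
- **The size of the shortfall depends on an assumed ICC and on the test.** This stands. With a normal test, 15 points keeps power above 0.80 up to an ICC of about 0.01. That test, however, treats the between-school variation as known when there are only two schools per arm. On 2 df and with the same standard deviation, 15 points has power of 0.87 at an ICC of exactly zero, but already 0.77 at 0.001.
- **Adjustment for baseline could reduce the variance between schools.** True, and the figures above are for an unadjusted comparison. Adjustment cannot add schools or degrees of freedom.
- **The study is exploratory and is placed between pilot and randomised trial.** Low power is acceptable there. But the article does not say that power is low. It claims 0.80 and a surplus. Its caution that a null result may reflect poor implementation is useful but does not concern power.
- **A journal article condenses.** A fuller calculation may exist elsewhere, but the inputs printed here reproduce the printed figure exactly and leave nothing for other inputs to explain.

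**Conclusion.** The concern holds. It is certain that the 500 follows from the model-size rule alone and carries no statement of power, and that the paragraph has no term for clustering despite a two-against-two school design. The statements about 0.80 power and about exceeding requirements are therefore unsupported as written.

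How far short the design falls rests on assumptions: equal schools of 375, standard deviation at 30% prevalence, no baseline adjustment, and ICCs of 0.005 to 0.05. Under these, power on 2 df is 0.30 to 0.09 for 10 points and 0.52 to 0.14 for 15 points. Neither end of the target reaches 0.80 anywhere in that ICC range. At the lowest ICC shown, the effective sample (523) is barely above 500; above an ICC of 0.0053 it is below. Because the paragraph makes an explicit claim about power that its own inputs do not support, it must be corrected.

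**What to change.** Rewrite the Power calculations section:

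1. Remove the link between 500 observations and a power of 0.80, and the statement that the sample exceeds what is needed. If the 500 is kept, label it as a rule for model size only.
2. Report the detectable difference for four schools of about 375 students over a stated ICC range, for example 0.005 to 0.05, using 2 school-level degrees of freedom and giving the outcome standard deviation used. If baseline adjustment is credited, state the assumed reduction in variance.
3. State that the trial is not powered for a 10–15 point change and serves to estimate effects, ICCs and feasibility for a later randomised trial. Describe subgroup analyses as exploratory, without appeal to a surplus.

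The cost is a change of text and a less favourable stated figure. Enrolling more students in the same four schools is not called for, since it would add little power.

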## Discussion

Recently several studies advocated the use of a *total life approach,* as promoted by SHE’s whole school approach. This approach aims to reach out beyond the borders of an adolescent’s ‘school life’ by incorporating the social environment(s), parents and the community [25, 27, 28]. Another aspect of this approach that is included in this approach is to make use of comprehensive interventions (including the creation of a healthy school environment and accordingly re-shaping behavioural policies) in contrast to ‘merely’ adding a standardized portion of health education to a given school curriculum/setting. The inclusion of a Healthy School Coordinator ensured that all whole school approach aspects were fine-tuned to and integrated within the school as well as with external parties. The most important aspect of this coordinating function is to steer the implementation and to guide the ‘tailoring process’ instead of implementing a highly standardized UHS. Both in the pilot study as well as in the current study the prioritization of the main *behaviours to tackle* and *outcomes to pursue* should be tackled by means of a questionnaire before and yearly after the start of the study. A recent successful large-scale example of such an approach was provided by Patton and all in their Gatehouse Project [48].

To stimulate the sustainability of the UHS, the schools did not receive external financial or organizational support and kept their complete autonomy and own internal structures. Taking into account the lessons learned from Flay [36], Campbell et al. [33], Pawson et al. [49], Campbell et al. [34] and Parsons and Stears [35] the first full year of the intervention was spent on internal organization and integrating the intervention *into* the pre-existing school practices and curriculum. A summary of the capacities that are needed for successful implementation of such a comprehensive health promoting school program as the UHS, a summary of Guggleberger and Dür’s recommendations on this account is presented below (Figure 3).

The aspect that creates the intervention’s potential success (its comprehensiveness) also creates potentially difficulties in analyzing its effectiveness. The variety of factors that make up the equation of the student’s health in the intervention schools makes it challenging to clearly distinguish between successful and unsuccessful characteristics of the program. The authors have tried to signal possible confounding effects by a thorough process evaluation on both intervention and control schools. Another limitation is the dependence upon self-reported student data. It proved infeasible to also collect parent/teacher data with respect to student health behavioural changes.

Strengths of the study are that within the intervention adolescent health is taken into account in a comprehensive manner, meaning that the focus was not placed merely upon one or two health topics, but on the understanding meaningful health promotion and education should entail the whole of health related behaviours in an integrated fashion. This differs significantly from the way health promotion and health education is commonly integrated into secondary schools in The Netherlands, namely via a disjointed, sporadic and non-evidence-based manner. Furthermore, the monitoring and annual feedback function of the student questionnaire aids to provide the schools with specific, tailored health promoting school policies.

